### Methods

The proposed study is a **randomized controlled trial (Figure 1)**. Participants will be randomly assigned to receive 2 training sessions (2 hours each) of either

**self-administered acupressure or knee health education** in 1:1 ratio. Participants in the self-administered acupressure group will be told to perform the self-administered acupressure twice a day for 12 weeks, and participants in the knee health education group will follow the knee health instruction every day for 12 weeks. Reminders for practice will be sent to the participants via WhatsApp. Outcome measures will be assessed at baseline, week 4, 8, and 12. Ethical approval from the institute will be sought before commencement of the study. We will follow the CONSORT and STRICTA for the report of the trial and acupressure protocol.

### Study design

Participants will attend two weekly 2-hour of self-administered acupressure training or knee health education according to the group allocation in a classroom at the School Nursing, the Hong Kong Polytechnic University. The participants will be trained to perform self-administered acupressure by an acupuncturist or receive knee health education by a registered nurse. To enhance interaction and ensure the quality of teaching, each class will be conducted in a small group of 4 to 6 subjects.

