## Supplement 1. Study Protocol

# Title: Self-administered Acupressure for Knee Osteoarthritis in Middle- and Older-Aged Adults: A Randomized Controlled Trial

## Abstract

**Objectives:** To evaluate the short- and medium-term effectiveness of self-administered acupressure taught by a short training course on reducing knee osteoarthritis (OA) pain in middle-aged and older adults.

**Hypothesis:** The self-administered acupressure group would have a greater pain relief compared to the knee health education (KHE) control in subjects with knee OA at week 12 (medium-term).

**Design and subjects:** In this fully-powered randomized controlled trial, 314 participants with knee OA recruited from the community will be randomized to self-administered acupressure or KHE group in a 1: 1 ratio.

**Study instrument:** Numerical rating scale (NRS) will be used to assess pain intensity in the knee.

**Interventions:** Participants in the self-administered acupressure will attend two 2-hour training sessions (1 week apart) to learn self-administered acupressure and practice twice daily for 12 weeks. Participants in the control group will receive knee health education of the same schedule and duration.

**Main outcome measures:** The primary outcome measure is the NRS score at 12 weeks. Other outcomes include Western Ontario and McMaster University Osteoarthritis Index, Short Form Six Dimensions, Timed Up & Go Test, Fast Gait Speed, pain medication usage. Compliance of self-administered acupressure will also be evaluated.

**Data Analysis:** Differences in the scale scores and test parameters will be examined using a linear mixed-effects model.

**Expected results:** Subjects in the self-administered acupressure group will have greater improvement in NRS and other related parameters compared to those in the KHE group at week 12.

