#### Fidelity of self-administered acupressure training by instructors

All the training materials will be reviewed and approved by the research team. A registered Chinese medicine practitioner with at least 5 years' clinical experience and at least a Master's degree will be recruited as an instructor to teach self-administered acupressure. The PA who is a senior acupuncturist, will go through the training materials with the instructor to ensure he/she understands the content and any pertinent details specific to the protocol. The instructor will run a demonstration course so that the PA and Co-A can assess whether the course content is being conveyed properly. PA will visit the first four classes and then randomly visit (at least one per month) to ensure the training content is adherence to the research protocol.

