#### Methods of randomization and allocation concealment

Block randomization with a random block size of 4 to 6 will be used to randomize eligible participants equally into the two groups. A computer-generated list of numbers known only to an independent administrator will be used in the randomization process. The group allocation will be enclosed in sequentially numbered opaque sealed envelopes. After the participants have finished all baseline assessments and the blinded assessor has confirmed their eligibility, then the independent administrator will give the participants a sealed envelope. The participants will then open the envelope to reveal their group allocation. The research assistant who is responsible for phone-call follow-up will then look at their opened envelopes to log the participants' code and allocation.

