## **5. Data processing and analysis**

### *Sample size calculation*

Results from our pilot study (N=35) of self-administered acupressure for knee OA are used for sample size calculations. At week 6, the mean (SD) of NRS in the self-administered acupressure group and knee health education group was 2.83 (1.47) and 2.07(1.58), respectively. It equals to an effect size of 0.49. With a more conservative approach, we use 80% of the effect size, which is 0.40 for the sample size calculation. A sample size of 133 subjects per group can provide 90% power to reject the null hypothesis with a significance level of 0.05. Assuming an attrition rate of 15%, a total of 314 subjects is required for this study.

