### *Data management and analysis*

All data will be double entered. All statistical analysis will be performed in SPSS (23.0) for Windows. Subjects' sociodemographic, clinical characteristics and baseline data was examined for potential group difference and any identified baseline difference was controlled as covariates. The changes of the primary outcome (NRS score) and other secondary outcomes were compared using linear mixed effects model with group (self-administered acupressure and knee health education) by time point interaction (baseline to week 12). Acceptability and compliance will be presented using descriptive statistics. Clinical significance will be examined by the proportion of participants who have a reduction of at least 2 points from baseline in the NRS using Chi-square test (25). The intention-to-treat analysis will be conducted.

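### Both arms are taught in classes of 4 to 6, but the 90% power assumes independent participants and the planned comparison names no class effect; any positive within-class correlation lowers power and makes a class-ignoring standard error too small.

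*Protocol*

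**What the plan says.** Allocation is individual: "Block randomization with a random block size of 4 to 6 will be used to randomize eligible participants equally into the two groups" (Protocol, Methods of randomization and allocation concealment). Delivery is by class: "each class will be conducted in a small group of 4 to 6 subjects" (Study design). That section gives closer interaction as one purpose of the small classes. The treatment descriptions add group training and joint practice for acupressure, and shared accounts of knee problems and class question time for the education control.

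The arms have different teachers. Participants are "trained to perform self-administered acupressure by an acupuncturist or receive knee health education by a registered nurse" (Study design), and a practitioner "will be recruited as an instructor to teach self-administered acupressure" (Fidelity of self-administered acupressure training by instructors), worded in the singular.

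The Sample size calculation takes a standardised effect of 0.40 and concludes: "A sample size of 133 subjects per group can provide 90% power to reject the null hypothesis". The only inflation is for 15% attrition, to a total of 314.

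Data management and analysis specifies a "linear mixed effects model with group (self-administered acupressure and knee health education) by time point interaction", with any baseline differences found entered as covariates. It does not describe the random effects and does not mention class. Clustering is not discussed anywhere in the protocol.

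**The concern.** Randomising individuals makes the arms comparable at baseline. It does not make outcomes independent once people are taught and practise together. Members of a class share its atmosphere, its discussion and how well those particular sessions went. The protocol itself, in its rationale for the control group, accepts that contact during teaching could affect pain.

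If this produces positive within-class correlation, the variance of an arm mean exceeds the independence value. Two things follow. The two-sample power calculation is optimistic. And an analysis that ignores class gives confidence intervals that are too narrow and a type I error above 5%. Recruiting more people in classes of the same size helps the first problem but not the second.

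**Working it through.** **Inputs from the protocol.** Class size 4 to 6 (midpoint 5, Study design); d = 0.40, α = 0.05, 90% power, 133 per group, 15% attrition, total 314 (Sample size calculation). Sidedness is not stated; two-sided reproduces the figure.

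**Assumption.** The protocol gives no ICC. I use 0.01 to 0.10 for illustration, the same in both arms.

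**Step 1: reproduce the plan's figure.** Under independence, n per arm = 2(1.960 + 1.282)²/0.40² = 131.3, so 132 by the normal approximation. The t-test version gives 132.3, so 133. Power at 133 per arm is 90.4% (normal) or 90.1% (t). Attrition: 133/0.85 = 156.5, so 157 per arm and 314 in total. The plan's figures reproduce exactly with no clustering allowance.

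**Step 2: add the class.** Design effect DE = 1 + (m − 1) × ICC; effective n per arm = 133/DE; power is then recomputed at d = 0.40. The type I error of a test that ignores class is 2[1 − Φ(1.96/√DE)]. For m = 5:

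| ICC | DE | Effective n | Power (normal / t) | SE too small by a factor of | Type I error, class ignored |
|---|---|---|---|---|---|
| 0.01 | 1.04 | 127.9 | 89.2% / 89.0% | 1.020 | 5.5% |
| 0.02 | 1.08 | 123.1 | 88.1% / 87.8% | 1.039 | 5.9% |
| 0.05 | 1.20 | 110.8 | 84.6% / 84.2% | 1.095 | 7.4% |
| 0.10 | 1.40 | 95.0 | 78.7% / 78.3% | 1.183 | 9.8% |

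Worked line for ICC 0.05: DE = 1 + 4 × 0.05 = 1.20; 133/1.20 = 110.8; 0.40 × √(110.8/2) = 2.98; Φ(2.98 − 1.96) ≈ 0.846.

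**Step 3: vary the class size.** Over m = 4 to 6, power (normal) is 88.9–89.5% at ICC 0.01, 83.1–86.0% at 0.05 and 75.9–81.6% at 0.10. If 15% attrition thins classes of 5 to 4.25 analysed members, power at ICC 0.05 is 85.7%.

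**Step 4: what restoring 90% would take (m = 5).** 133 × DE gives 139 per arm at ICC 0.01, 160 at 0.05 and 187 at 0.10. With 15% attrition the totals are 328, 378 and 440. This shows scale only; it is not a proposal to enlarge the trial.

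**The case against.** The case against is substantial.

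- **The ICC may be very small.** Class contact is two 2-hour sessions. The outcome is each person's own knee pain at week 12, after practice at home twice a day. Technique is checked person by person, calls and messages reach participants outside class, and acupressure teaching is standardised and monitored. At ICC 0.01 the loss is about one point of power and half a point of type I error. This stands, and it is why the harm can only be stated conditionally.
- **The model is only summarised.** The protocol calls it a mixed-effects model, leaves the random effects undescribed and allows baseline covariates. A statistical analysis plan, not shown here, could include class. This stands for the standard-error half of the point. It does not rescue the power statement, which the protocol makes in full and which assumes independence.
- **The power figures are for a simpler analysis.** They apply a two-sample comparison. The mixed model uses baseline. If d refers to week-12 scores (an assumption), a baseline correlation r scales the variance by about 1 − r², so r ≈ 0.41 would offset a design effect of 1.20 (1 − 0.41² ≈ 0.83 ≈ 1/1.20). This stands as a possible recovery of power. It does not correct the error rate of an analysis that ignores class.
- **The effect size was already reduced from 0.49 to 0.40.** The protocol offers this as general caution about the effect, not as an allowance for clustering, so it does not answer the point.

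A reader might also take the shared instructor as the source of clustering. The documents do not support that. The arms have different teachers, and if one person teaches all classes in an arm, that person's effect is confounded with arm and creates no variation between classes within it. The cluster is the class.

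**Conclusion.** The point holds in conditional form. The protocol creates classes in both arms, states 90% power on an independence basis and names no class effect in its comparison. Whenever within-class correlation is positive, power under that calculation is below 90% and an analysis ignoring class is anti-conservative. On the assumed ICC range the effect runs from negligible to material.

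Two stronger readings are tempting. One is that the trial is underpowered and its standard error wrong as a matter of fact. The documents give no ICC, and at the low end almost nothing changes. The other is that the primary model excludes class. The protocol is silent on its random effects, which is not the same thing.

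The change should be made, but the main analysis does not fail without it. Confidence is medium, because the size depends on a parameter that the documents do not supply.

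**What to change.** 1. **Record a class identifier** for every participant at delivery. Training attendance is already to be recorded, so this adds one variable.
2. **Add a random intercept for class, nested in arm,** to the primary and secondary mixed models, with small-sample degrees of freedom such as Satterthwaite. Classes first meet after baseline. If baseline stays in the model as a response, the class effect should act on the post-baseline visits only; an intercept shared with baseline would cancel out of the change contrast. With 157 randomised per arm there would be about 26 (157/6) to 39 (157/4) classes per arm, enough to estimate a class variance.
3. **Allow for class elsewhere.** Use a class-robust or mixed-model version of the responder comparison, and resample whole classes within arm in the economic bootstrap.
4. **Keep 314 and restate the power.** Replace the unconditional 90% with power over a stated ICC range, for example about 89% at 0.01, 84–85% at 0.05 and 78–79% at 0.10 for classes of 5. Say that this is before any gain from baseline adjustment.

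The cost is one recorded variable, some wording, slightly wider intervals and a slightly lower stated power. No participants are added, and randomisation, endpoint and delivery are unchanged.

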### Treatment protocol

#### *Self-administered acupressure treatment group*

Participants in this group will receive two acupressure training sessions (2 hours each, 1-week apart). The self-administered acupressure treatment protocol was developed based on TCM meridian theory by the previous studies (10, 11) and modified by the PA who is an experienced acupuncturist. The acupoints are indicated for knee pain and have been commonly used (13). The protocol was tested for feasibility in our pilot study. We have modified the treatment protocol after the pilot study to further enhance the effectiveness and compliance of acupressure, including sending video on steps of locating acupoints and technique of acupressure to the participants via WhatsApp and incorporating a brief knee health education in the second session.

During the **1st session** (initial training), each participant will then receive a handout and an acupressure logbook. The handout includes a picture-illustrating acupressure step-by-step protocol. The acupressure logbook is for them to record their acupressure practice every day. The instructor will give a brief introduction about acupressure (20 minutes), followed by a group training on locating acupoints and manipulating acupressure technique (30 minutes). The treatment protocol consists of 4 steps (10, 11), namely warm-up, acupressure (on acupoints ST34, ST35, ST36, SP9, SP10, GB34, EX-LE2, and EX-LE4), rubbing the knee, and move the knee. The acupressure exercise takes about 16 minutes. The participants will then practice the acupressure (30 min), and then the instructor will inspect their performance of acupressure using a

competency checklist (30 minutes). The instructor will give feedback to their practice. Finally, the instructor will give a summary and answer queries (10 min). Additional training and practice time may be given to those who have not met the requirement in the checklist.

Participants will be asked to perform the acupressure exercise at home in the morning (within 1 hour after wake up) and night (within 1 hour after dinner) every day for 12 weeks. Participants will receive 2 follow-up phone calls from the instructor during the first week to remind their practice and answer their queries.

The **2nd session** (refreshing training) will be conducted 1-week after the first session (2nd week). The instructor will **revisit** the theory of acupressure and addressed issues raised by the subjects during their past week at-home practice (20 minutes). Participants' acupressure logbook will also be examined. The participants will be asked to have a **group practice** the self-acupressure (30 minutes), followed by a **brief knee health education** (30 minutes). Finally, the training will be concluded by a final practice and **fidelity check** by the instructor (30 minutes) and **Q&A** (10 minutes).

#### Fidelity of self-administered acupressure training by instructors

All the training materials will be reviewed and approved by the research team. A registered Chinese medicine practitioner with at least 5 years' clinical experience and at least a Master's degree will be recruited as an instructor to teach self-administered acupressure. The PA who is a senior acupuncturist, will go through the training materials with the instructor to ensure he/she understands the content and any pertinent details specific to the protocol. The instructor will run a demonstration course so that the PA and Co-A can assess whether the course content is being conveyed properly. PA will visit the first four classes and then randomly visit (at least one per month) to ensure the training content is adherence to the research protocol.

#### Fidelity of self-administered acupressure in participants

The capability of participants for self-administered acupressure will be inspected by the instructor with a **competency checklist** in each session. The practice of self-administered acupressure will be assessed in four domains: accuracy of locating acupoints, acupressure technique, strength, and frequency of acupressure at each acupoint. Advice and correction will be made when necessary. Video on steps of locating acupoints and instruction on the technique of acupressure will be sent to the participants via WhatsApp for their reference at home. A contact phone number will be available for participants to contact the research assistant if they have any queries regarding the acupressure. Participants' acupressure technique will be assessed again at week 4.

### Monitoring of compliance at home (Intervention group)

Participants will receive an acupressure logbook to record the time and duration of their daily practice. Checklists for the correct performance of each step or skill will be available with the acupressure logbook to maximize the fidelity of self-administered acupressure. Telephone follow-up will be conducted by the instructor to remind them to practice and answer queries regarding the acupressure during the first week. Reminders will be made twice a week via WhatsApp by the research assistant during the remaining study period to remind subjects to practice self-acupressure.

### *Knee health education control group*

Participants in this group will receive two sessions (2 hours each) of health education related to knee OA symptom management. The course content is developed from the course materials from the websites of Elderly Health Service, Department of Health, Hong Kong SAR (19) and reviewed by the CoA who is a physiotherapist.

During the 1st session, the instructor will invite the participants to share their knee problems and their experiences (30 minutes). The education will cover introduction to the causes, presentation and symptoms of knee OA (30 minutes). Prevention and self-care for the deterioration of knee OA will be introduced and explained to the participants (30 minutes). At the end of the session, all the subjects were encouraged to ask questions regarding the education content (15 minutes). The instructor will conclude the session with a summary and ask the participants to follow the prevention and self-care instruction taught in the class (15 minutes). A handout summarized the content of health talk and a logbook for recording daily pain management will be distributed to the participants.

During the 2nd session, the participants will be encouraged to raise questions regarding their practice of knee health instruction at home and difficulties came across during the past week (15 minutes). Followed by a revision of the content of the first session (30 minutes). The instructor will introduce available treatments and routine care for knee OA, including exercise, weight loss, medications, and diet regimen of Chinese medicine (30 minutes). The participants will have a 10-items multiple choices test to ensure they have understood the course content. The instructor will go through each item with explanation on the correct answer (30 minutes). The training session will be adjourned after all participants demonstrate an understanding of the instructions after a final Q&A section (15 minutes).

As a compensation, participants in knee health education group will receive the same self-administered acupressure training after completion of the 12-week assessment.

#### Monitoring of compliance at home (Control group)

Similar to the self-administered acupressure group, telephone follow-up will be conducted by the instructor to remind them to follow the instruction and answer queries regarding the education content during the first week; reminders will be made twice a week via WhatsApp by the research assistant during the remaining study period to remind subjects to follow the instruction. Participants will record whether they have followed the knee health instructions in a logbook.

#### Rationale of the control group

Since acupressure training involves much contact time between the instructor and participants, the improvement in participants' pain, if any, may be attributed to non-specific effects from the subject-practitioner interaction. Care as usual and waitlist control used in previous studies are not able to control for such non-specific effects and even lead to placebo effects due to "not being treated". Therefore, in this proposed study, knee health education for the same length as in the self-administered acupressure group is adopted to control the contact hours between the instructor and participants. If our self-administered acupressure training is found to be more effective than education, then it can be examined in further studies to compare with other standard interventions or exercise programs.

#### Concomitant treatments

All the participants are allowed to keep their routine medical care for knee osteoarthritis provided by the public or private healthcare service in Hong Kong.

